#### Data analysis primary outcomes

Study data are collected by clinical research assistants and managed using REDCap electronic data capture tools at the lead institution site (Rush University Medical Center). REDCap (Research Electronic Data Capture) is a secure, web-based software platform designed to support data capture for research studies, providing 1) an intuitive interface for validated data capture; 2) audit trails for tracking data manipulation and export procedures; 3) automated export procedures for seamless data downloads to common statistical packages; and 4) procedures for data integration and interoperability with external sources [36].

Chi square and t-tests will be used to measure differences in baseline characteristics of both groups. Linear mixed effects modeling will be used to measure differences in the outcomes associated with ASES scores, pain, SANE, and range of motion measures across all time points. Linear mixed effects modeling is robust to individual changes, allows for control of variables that are different at baseline, and allows for control of variables that influence outcomes. Linear mixed effects modeling is not bound by the same assumptions as OLS modeling methods (e.g., ANOVA). Differences will be captured for up to 6 time points (pre op to post at 2 and 6 weeks, 3, 6, 12 and 24 months). A *p* value of < 0.05 will be considered statistically significant for all analyses.

We will evaluate the primary outcomes with two sets of statistical analyses: One with intention to treat including patients who crossed over and a second adjusted to the cross-overs of the patients. Non-adherence to randomly assigned treatments can often mean that the intention-to-treat analysis underestimates the real benefit of the treatment [48]. We will run a preplanned sensitivity analysis evaluating the descriptive statistics of those who crossed over to those who did not. We will also run an estimated “as treated” longitudinal analysis based on comparisons of those actually treated with PT and HT. We will analyze a repeated measures, linear mixed effect model in which our outcomes will remain the dependent variable and treatment received will be incorporated as a time varying covariate. Adjustments will be made for the time of cross-over with respect to the original enrollment date to approximate the designated follow-up times. Baseline variables that were individually found to predict missing data or treatment received will be included to adjust for possible confounding.

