### Eligibility criteria/subjects

Participants are identified as potential subjects for this study if they are over 50 years of age, under the care of one of the participating surgeons, and elect to have RTSA for rotator cuff tear arthropathy, massive irreparable rotator cuff tear, or primary osteoarthritis. Subjects are excluded from study participation for the following reasons: history of prior ipsilateral open shoulder surgery, non-reverse total shoulder arthroplasty, RTSA for fracture or revision arthroplasty, RTSA with a tendon transfer, discharge to a skilled nursing facility, in-patient rehabilitation placement, or use of home health therapy prior to progressing in recovery, unwilling to make a good faith effort to adhere to their randomly prescribed rehabilitation scheme, unable to speak, read, or write the English language, have cognitive deficits limiting ability to follow direction, unable or unwilling to be randomised due to financial or personal constraints, or have inability to attend physical therapy (i.e. transportation or financial limitations). Subjects who meet the inclusion criteria are identified at clinical appointments with participating surgeons, and clinical research assistants discuss the study process and review the voluntary informed consent process. At this appointment the following variables are obtained as pre-operative baseline values: American Shoulder and Elbow Surgery (ASES) score, Numeric Pain Rating Scale (NPRS) level, Single Assessment Numeric Evaluation (SANE) score, active range of motion (AROM), passive range of motion (PROM), and Patient-Reported Outcomes Measurement Information System (PROMIS) score. Upon voluntary consent to participate, clinical research assistants employ computer based Research Electronic Database Capture (REDCap) (Nashville, TN) [36] to perform the allocation sequencing of subjects to either the PT or HT group. The randomization schedule is a randomized block design stratified by site using a 1:1 treatment allocation in blocks of size 8.. Patients are encouraged to remain within the group to which they are randomly assigned for the duration of the study, however, if the patient, surgeon, or therapist has concern regarding patient safety, compliance or outcome due to the group assignment, cross-over to the other group will be allowed. The research plan is for approximately a 15% crossover rate based on prior research which planned for 10%, but actually ended up with 30% crossover [37]. The reason for cross-over will be recorded in the electronic health record and reported in the study result.

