### Statistical analysis

#### Sample size

To determine sample size of this parallel design, the study was powered (a-priori) for the primary outcome measure of the American Shoulder and Elbow Surgeon (ASES) scale at baseline, 2 and 6-weeks, 3 and 6 months post replacement. Study assumptions estimate a 12 month ASES score of 79/100 for the PT group (SD = 15.0) and 69/100 for the HT group (SD = 15.0). The 10 point change is considered a clinically meaningful difference in groups [10].

Assuming normal distributions among the 2 independent group ASES measures, and assuming small-to-medium effect based on between-group differences, we constructed a sample size estimation using a Repeated Measures Analysis of Covariance (ANCOVA). Measuring fixed effects, main effects, and interactions, with an expected 80% power, 6 dedicated time intervals (including baseline), two independent groups, 2 covariates, 1 outcome measure, and a standard error of probability of 0.05, we estimate the need for a minimum sample size of 158 for statistical significance (~ 79 per group). To account for the expected potential 24 crossover (15%) subjects, we will increase enrollment to 182 total. Missing values will be adjusted using a chains equation, multiple imputation method in which we will assign predictor, structural and impute variables.

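### The primary ASES model leaves the treatment contrast and the role of the pre-operative score open, invites covariate choice from baseline tests, and does not mention site

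*Protocol article*

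**What the plan says.** Three sections of the protocol article bear on this.

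- **Sample size.** The design effect is 79 against 69 ASES points at 12 months, SD 15 in each group. The calculation is a repeated measures ANCOVA with "6 dedicated time intervals (including baseline), two independent groups, 2 covariates, 1 outcome measure". The two covariates are not named. Main effects and interactions are both mentioned, without saying which one is the treatment test.
- **Data analysis primary outcomes.** The mixed model covers ASES, pain, SANE and "range of motion measures across all time points". The occasions are then given as "Differences will be captured for up to 6 time points (pre op to post at 2 and 6 weeks, 3, 6, 12 and 24 months". The same paragraph states "Chi square and t-tests will be used to measure differences in baseline characteristics of both groups" and adds that the mixed model "allows for control of variables that are different at baseline, and allows for control of variables that influence outcomes". No covariate is listed.
- **Eligibility criteria/subjects.** "The randomization schedule is a randomized block design stratified by site", with 1:1 allocation in blocks of 8. The abstract gives seven sites. Site is not mentioned anywhere under Statistical analysis.

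**The concern.** Three things are left loose in the analysis that decides the trial.

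1. **Baseline and the contrast.** Randomisation makes the expected arm difference zero before surgery. If the pre-operative score is an ordinary outcome occasion and the test is a group main effect, that zero is averaged into the treatment effect. If the test is something else, the text does not say what, although the effect was specified at 12 months and the Background hypothesises both faster recovery and better long-term recovery. Those are visit-specific questions.
2. **Covariates.** Between randomised arms, a baseline significance test can only detect chance. Placing such tests beside a remark about controlling for variables that differ invites a model that depends on which variables happened to differ. A strongly prognostic variable such as baseline ASES could be left out because the arms were well balanced on it.
3. **Site.** Stratified blocks balance the arms within site. A model without site leaves between-site variation in the residual and does not collect the precision that the design bought.

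**Working it through.** **The plan's own figure.** A noncentral-F ANCOVA calculation with two groups, two covariates, alpha 0.05 and 80% power gives N = 158 when f = 0.25 and the numerator degrees of freedom are 2. Both values are inferred; neither is stated. With f = 0.25, one numerator degree of freedom gives 128 and five give 211. A two-group main effect has 2 − 1 = 1 degree of freedom, and a group-by-occasion interaction over six occasions has (2 − 1)(6 − 1) = 5. The value that reproduces 158 is neither, so the sample size does not reveal which contrast is meant.

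**Inputs.** From the article: difference 10, SD 15, 79 per arm, seven sites, 182 patients after the crossover allowance. Assumed: the same SD and the same correlation r between any two visits, an effect that is constant after surgery, an intraclass correlation (ICC) for site, and no loss to follow-up.

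**Step 1: averaging over visits.** With pre-op and six post-operative visits, the mean difference is 10 × 6/7 = 8.57. With five post-operative visits it is 10 × 5/6 = 8.33. With a group-by-visit contrast it stays at 10.

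For a group main effect over seven occasions, SE = 15 × √((1 + 6r)/7) × √(2/79). For the mean of the six post-operative visits adjusted for baseline, SE = 15 × √((1 + 5r)/6 − r²) × √(2/79). Power is two-sided at 5%.

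| r | SE, pre-op averaged in | SE, baseline-adjusted | Power at a true 5 points: averaged in | Power at a true 5 points: adjusted |
|---|---|---|---|---|
| 0.3 | 1.51 | 1.36 | 81% | 96% |
| 0.5 | 1.80 | 1.38 | 66% | 95% |
| 0.7 | 2.06 | 1.22 | 55% | 98% |

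At the assumed 10 points, power is at least 98% in every row either way.

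**Step 2: the 12-month contrast.** Relative to a baseline-adjusted contrast, whose variance is proportional to 1 − r²:

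- change from baseline keeps (1 − r²)/(2(1 − r)) = (1 + r)/2, which is 70% at r = 0.4 and 80% at r = 0.6;
- an unadjusted contrast keeps 1 − r², which is 84% at r = 0.4 and 64% at r = 0.6.

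The unadjusted SE is 15 × √(2/79) = 2.39, so z = 10/2.39 = 4.2 and power is about 99%. The least favourable of these cases, change from baseline at r = 0.4, has SE 2.39 × √1.2 = 2.61, z = 3.8 and power about 97%.

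**Step 3: site.** Simulation with seven sites of 26 patients (7 × 26 = 182), balanced within site:

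| Assumed ICC | SE without site | SE with site | Excess | Type I error without site |
|---|---|---|---|---|
| 0.02 | 2.22 | 2.20 | 1% | 0.049 |
| 0.05 | 2.21 | 2.16 | 2% | 0.049 |
| 0.10 | 2.20 | 2.11 | 5% | 0.040 |

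**Step 4: baseline tests.** The Descriptive information section lists 11 variables: age, sex, height, weight, dominance, laterality, indication, prior surgery, prior fracture, prior dislocation and prosthesis type. Tested at 5% and treated as independent, the chance of at least one significant difference is 1 − 0.95¹¹ = 43%. Height, weight and sex are correlated, so this is approximate. Baseline ASES would be flagged only if the observed arms differed by more than 1.975 × √(2/79) = 0.31 SD.

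**The case against.** A reader might infer that the plan does dilute the effect, does pick covariates by significance, and decides to leave site out. The text does not support those readings.

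- **Dilution.** It needs a single main effect over visits that include pre-op. The sample size section also mentions interactions. The list of occasions can be read as six pre-to-post differences, which makes the count of six correct and pre-op a reference. Keeping baseline in the response of a longitudinal model is also an accepted approach if the contrast is suitable. A larger shrinkage, to 50/7 = 7.1 points, would need a zero effect at 2 weeks. The article gives no figure for that visit, and PT starts 4-5 days after discharge.
- **Covariates.** The wording is permissive and names variables that influence outcomes alongside those that differ. No sentence says that a significant test admits a covariate. The explicit data-driven inclusion rule in that section follows the as-treated analysis. The 43% and 0.31 SD figures apply only if such a rule were used.
- **Site.** Its absence is silence in a condensed article with two unnamed covariates, and a full model may sit in an analysis plan not shown here. The effect on the standard error is small and conservative, so a charge of misstated precision would be too strong.
- **Power.** At the design effect nothing material is lost.

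All of this stands, and it sets the size of the point. It does not remove the point: baseline is expressly counted as a repeated occasion, baseline tests of randomised arms are expressly planned, and none of the readings on offer is stated to be a baseline-adjusted contrast at the visit used for sizing.

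**Conclusion.** The point holds as one of unfixed choices and avoidable inefficiency, not as a demonstrated bias. Under a main effect over all visits, 10 points would be estimated as about 8.6; under a group-by-visit contrast there is no dilution. A 12-month contrast without baseline adjustment, or on change scores, keeps about 64-84% of the available information for r between 0.4 and 0.6. Omitting site costs about 1-5% in standard error for an ICC of 0.02-0.10. Correlations, ICC, equal SD across visits and the constant post-operative effect are assumptions, and losses and crossover are ignored. Since power at 10 points stays high on every reading, the benefit lies in a tighter interval, better protection if the true difference is nearer 5 points, and a result that cannot depend on chance baseline differences. The change should be made; the trial's conclusion does not hang on it.

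**What to change.** State the primary model in the protocol or analysis plan, before arm-level data are examined:

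- a mixed model for ASES with visit, arm-by-visit, baseline ASES as a covariate (or a pre-operative mean constrained equal across arms), and site as a fixed factor;
- a few prognostic covariates named in advance, for example surgical indication, age and sex;
- PT minus HT at 12 months, the visit of the sizing assumption, as the primary contrast, with other visits as supporting contrasts;
- baseline characteristics reported descriptively, with no covariate chosen from baseline tests;
- one reconciled count of occasions across the two sections, saying whether pre-op is among them.

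The cost is wording and six degrees of freedom for seven sites. All the variables are already collected, and the sample size need not change.

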#### Data analysis secondary outcomes

##### Complications analysis

The complication rate is defined as the incidence of the occurrence of the complication divided by the total number of subjects in the PT or HT group, expressed as a percentage. Statistical difference between the two groups will be compared between the PT and HT groups using a Chi Square test with level of significance *p* < 0.05.

##### Quality of life and cost analysis

To analyze quality of life and cost-effectiveness differences between the PT and HT groups, two formal steps will be followed. Step one will involve a crosswalk of PROMIS 29.2 measures to EQ5D quality of life measures, [49] which is a standardized utility measure. Utilities are measured on a cardinal scale of 0–1, where 0 indicates death and 1 indicates full health. Using the ‘anchors’ of 0 and 1, utility measurement is on an interval scale, where the same change means the same irrespective of the part of the scale being considered (e.g. a change in health from 0.2 to 0.3 is equivalent to a change from 0.8 to 0.9). States worse than death can also be accounted for, with such states taking a negative value [50]. We will use the formula by Revicki and colleagues to complete the crosswalk [51].

*EQ5D = (1.0266+0.0077) X (PROMIS physical functioning t score -0.0021) X (PROMIS fatigue t score – 0.0040) X (PROMIS pain interference t score – 0.0023) X (PROMIS anxiety t score-0.0022) x (PROMIS depression t score)* [49]

The formulaic calculations will result in a quality -adjusted life year value (QALY). QALY’s reflect two key elements—health related quality of life and survival. QALYs can be aggregated across individuals, i.e., a QALY is a QALY regardless of who gains/loses it. Differences in the QALY between the PT and HT groups will be assessed using a Mann Whitney U test with a level of significance considered *p* < 0.05.

Step two will involve cost-effectiveness of the interventions. Cost effectiveness studies usually provide the result in the form of an incremental cost-effectiveness ratio. Total charges for PT and HT groups will be estimated using mean charges for the billable units at each of our collection locations. Total charges of care will be calculated against the QALY identified in step one to determine the cost of 1 QALY using the modeling method of Riesco-Martínez et al. [52] For example, if the average total cost of PT is $10,000 USD, and the average QALY for patients receiving PT was 0.79, the total costs for 1 QALY would be calculated as $10,000 USD / 0.79 (average QALY), or $12,658 USD/QALY. We will compare PT charges to the HT group charges using a Mann Whitney U test with level of significance of *p* < 0.05.

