We aim to compare outcomes for formal, clinic-based physical therapy (PT group) to home therapy, in which patients are provided with instructions from surgeons at post-operative appointments (HT group) by using a superiority, randomised design [34]. Findings will aid in determining the potential role of formal PT in the RTSA recovery process, and secondarily, will evaluate a formal RTSA rehabilitation protocol, which is standardized for the trial [20].. Findings from the study may assist in evaluating the financial benefit or burden of formal PT in the RTSA recovery process and determine the resource necessity of PTs in a traditional clinical environment. We hypothesize that the PT group will demonstrate superior clinical and patient reported outcomes, significantly quicker levels of recovery, and significantly higher levels of overall recovery at our long-term outcomes capture when compared to the HT group. Secondary aims of this project include analysis of the incidence of complications between the two groups, specifically acromial stress fractures and prosthetic instability events, which we hypothesize will be higher in the PT group; and cost of care which we hypothesize will be higher in the PT group.

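### The PROMIS-to-EQ-5D crosswalk is printed as a product of five T-scores, so it cannot give a 0–1 utility and can reverse the QALY comparison

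*Protocol article*

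**What the plan says.** The section on quality of life and cost analysis (protocol article, secondary outcomes) sets out two steps.

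Step one converts PROMIS-29 scores to an EQ-5D utility. The target scale is stated: "Utilities are measured on a cardinal scale of 0–1, where 0 indicates death and 1 indicates full health", with negative values allowed for states worse than death. The equation opens "EQ5D = (1.0266+0.0077) X (PROMIS physical functioning t score -0.0021) X (PROMIS fatigue t score" and closes "X (PROMIS anxiety t score-0.0022) x (PROMIS depression t score" followed by the last bracket. The sentence that introduces it cites reference 51; the equation itself is tagged with reference 49. The output is then used directly: "The formulaic calculations will result in a quality -adjusted life year value (QALY"). The arms are compared on it by rank: "Differences in the QALY between the PT and HT groups will be assessed using a Mann Whitney U test".

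Step two divides charges by that value. The worked example is "the total costs for 1 QALY would be calculated as $10,000 USD / 0.79 (average QALY), or $12,658 USD/QALY".

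No other part of the article gives the crosswalk in a different form.

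**The concern.** The constants look like an intercept and five regression weights, but the brackets and multiplication signs do not use them that way. As printed, the intercept and the physical function weight form one constant, 1.0343. The other four weights are tiny amounts taken off T-scores, and all five T-scores are multiplied together.

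Two things follow. The size of the result cannot match a utility. The direction is also wrong for four of the five domains, because a larger symptom score enlarges the product. The second matters more for the planned test: a Mann-Whitney comparison is not disturbed by an absurd scale, but it is disturbed by a wrong ordering of patients.

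This equation is the only stated route from PROMIS-29 to the utility, the QALY and the cost per QALY, so the whole cost-effectiveness aim rests on it.

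**Working it through.** **Inputs from the article.** The five constants, their signs and the bracketing; the 0–1 scale; the example of $10,000 and 0.79.

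**Assumptions not in the article.** T-scores centre near 50 and are examined over 30 to 70. A higher score means better physical function (PF) but worse fatigue, pain interference, anxiety and depression.

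**The plan's own figure.** 10,000 / 0.79 = 12,658, as stated. So the example is arithmetically sound and presupposes a divisor below 1.

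**Two forms compared.**

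- Printed: 1.0343 × (PF − 0.0021) × (fatigue − 0.0040) × (pain − 0.0023) × (anxiety − 0.0022) × depression
- Weighted sum of the same constants: 1.0266 + 0.0077 PF − 0.0021 fatigue − 0.0040 pain − 0.0023 anxiety − 0.0022 depression

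With every score at 50:

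- Printed: 1.0343 × 49.9979 × 49.9960 × 49.9977 × 49.9978 × 50 = 3.23 × 10⁸
- Sum: 1.0266 + 0.385 − 0.105 − 0.200 − 0.115 − 0.110 = 0.8816

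| Profile (PF / fatigue / pain / anxiety / depression) | Printed | Weighted sum |
|---|---|---|
| 50 throughout | 3.23 × 10⁸ | 0.882 |
| 30 throughout | 2.5 × 10⁷ | 0.940 |
| 70 throughout | 1.7 × 10⁹ | 0.824 |
| Healthier: 55/45/45/45/45 | 2.33 × 10⁸ | 0.973 |
| Sicker: 40/55/65/55/55 | 4.47 × 10⁸ | 0.712 |
| Pain 60, others 50 | 3.88 × 10⁸ | 0.842 |
| PF 55, others 50 | 3.56 × 10⁸ | 0.920 |
| PF 55, pain 45, others 50 | 3.20 × 10⁸ | 0.940 |
| PF 60, pain 45, others 50 | 3.49 × 10⁸ | 0.979 |
| PF 60, all symptoms 40 | 1.59 × 10⁸ | 1.065 |

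**Size.** For the printed form to equal 0.79 with equal scores, each would have to be about (0.79 / 1.0343)^(1/5) = 0.95. At $10,000 and scores of 50, the cost per QALY would be 10,000 / (3.23 × 10⁸), about $0.00003.

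**Direction.** Near 50, one point on any domain changes the product by about 2%, upward whenever the score rises. An overall improvement therefore lowers the printed value roughly when the symptom points gained, summed over four domains, exceed the PF points gained. The table shows both sides: the sicker profile outranks the healthier one, but a gain in PF alone, or a PF gain of 10 with a pain gain of 5, moves the right way.

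In simulated patients (mean 50, SD 10, scores held within 20 to 80), the two forms ordered 54%, 77% and 83% of pairs oppositely at between-domain correlations of 0, 0.5 and 0.7.

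**Cost per QALY.** The ordering of the arms depends on the PT/HT charge ratio relative to the PT/HT QALY ratio. Suppose PT is 5 points better on every domain, from 50. The QALY ratio is 0.973 / 0.882 = 1.10 by the sum and 0.72 by the product, so the ordering differs only if the charge ratio lies between 0.72 and 1.10. If HT is 5 points better, the ratios are 1 / 1.10 = 0.91 and 1 / 0.72 = 1.39, and the ordering differs only between those values.

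**The case against.** The strongest reply is that this is a conspicuous transcription error. The text says a published formula will be used, each constant sits directly before a multiplication sign and a score, and the 0.79 example shows that a 0–1 result was intended. An analyst who obtained a utility of 300 million would stop. That stands as far as it goes: the harm arises only if the line is coded as printed, and the repair is easy. It does not make the equation correct, and nothing else in the article corrects it.

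A reader might infer that the QALY comparison would be reversed. The article does not support that. Physical function also enters the product as a positive factor, so the outcome depends on which domains separate the arms. The contrast between the sicker and healthier profiles moves every domain against the patient at once, which is the case most prone to reversal.

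A reader might also infer that the cost-per-QALY ordering would reverse. That needs a charge ratio fairly close to 1. The article gives no charge ratio and says only of "cost of care which we hypothesize will be higher in the PT group" that PT is expected to be the dearer arm.

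The centre, range and direction of the T-scores are assumptions here. The scale violation survives any T-scores in the tens; the argument on direction needs the stated direction of the symptom scales.

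**Conclusion.** The equation is wrong as written and has to be corrected before any QALY or cost-per-QALY analysis. Under the assumed T-scores of 30 to 70 it yields about 2.5 × 10⁷ to 1.7 × 10⁹, against a scale "where 0 indicates death and 1 indicates full health", and it increases with all four symptom scores. Coded literally, the cost per QALY is meaningless in size. The rank comparison of QALYs can reverse when symptom differences dominate and keeps its direction when physical function drives the difference. Reversal of the cost-per-QALY ordering is possible but not established.

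The damage is confined to the utility, QALY and cost-effectiveness results. The ASES analysis on which the trial is powered and the complications comparison do not use this equation.

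**What to change.** Replace the printed equation with the weighted sum that its constants imply:

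EQ5D = 1.0266 + 0.0077 × physical function − 0.0021 × fatigue − 0.0040 × pain interference − 0.0023 × anxiety − 0.0022 × depression

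This form is inferred from the printed constants. Confirm every coefficient and sign against the cited source first, and state whether that source is reference 49 or 51.

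Add two checks to the analysis code. One confirms that the computed utility rises with physical function and falls with each symptom score. The other flags implausible utilities for review. It should not reject values slightly above 1, because the weighted sum itself gives 1.065 at PF 60 with all symptoms at 40.

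The cost is one corrected equation, one clarified citation and a few lines of code, with no change to data collection. The corrected equation gives a utility, which the section still labels a QALY; correcting the crosswalk does not by itself settle that step.

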##### Physical therapy intervention group

Subjects in the PT group will begin out-patient clinic-based rehabilitation 4–5 days after discharge from the hospital and continue in therapy approximately once a week for three months. Physical therapists will employ a pragmatic approach within the rehabilitation guidelines summarized in Table 1. Physical therapists will determine the optimal exercises for each patient within the specified guidelines for each phase of recovery. The exercises may vary amongst subjects considering patient specific variables such as exercise tolerance and pain response, ease of progressing to next level of challenge, ability to follow directions and perform exercises correctly, and individual goals for rehabilitation. The number of physical therapy visits may vary amongst patients in this group depending on response to therapy. For example, patients with low demand goals for rehabilitation and/or those who tolerate therapy well and advance easily may need less PT visits than patients with high demand goals and/or those who don’t tolerate therapy well and progress more slowly.

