##### Home therapy group

Patients continue to perform the exercises they learned in the hospital prior to discharge until they follow-up with the surgeon per the standard of care approximately 2 weeks after surgery. Rehabilitation exercises and activity guidelines will be advanced for the HT group by the treating surgeon using pre-printed exercise handouts which follow the rehabilitation guidelines in Table 1. The handouts will not vary amongst subjects for consideration of patient specific variables. All subjects will receive the same exercise progression at the 2 week, 6 week, and 3 month appointment.

Additional physical therapy following the RTSA procedure (not in the PT or HT group) will not be allowed. Other physical care such as chiropractic or massage intervention for conditions not related to the RTSA procedure will be allowed upon approval by the treating surgeon.

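### The only test of the cost hypothesis is a rank test on charges, which does not compare mean cost; how far it misleads depends on which charges are counted

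*Protocol article*

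**What the plan says.** The Background states the secondary hypothesis as "cost of care which we hypothesize will be higher in the PT group". The section Quality of life and cost analysis then describes three things:

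- **How charges are built:** "Total charges for PT and HT groups will be estimated using mean charges for the billable units at each of our collection locations".
- **How they are used:** "Total charges of care will be calculated against the QALY identified in step one". The worked example begins "if the average total cost of PT is $10,000 USD, and the average QALY for patients receiving PT was 0.79", so the reported figure is a mean cost over a mean QALY.
- **How the arms are compared:** "We will compare PT charges to the HT group charges using a Mann Whitney U test", at the 0.05 level. No comparison of mean cost and no interval is stated.

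Two passages determine therapy use by arm. PT patients start clinic therapy within days of discharge and "continue in therapy approximately once a week for three months". For HT patients the rule is "Additional physical therapy following the RTSA procedure (not in the PT or HT group) will not be allowed", so they have therapist visits only if they cross over.

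The section Costs and complications data names two cost inputs: the number of therapist visits, for the PT group, and physical therapy reimbursement from a payer database. Complications and unanticipated presentations are recorded, but no price source is named for them.

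**The concern.** The hypothesis and the cost-per-QALY figure concern mean cost of care. The Mann-Whitney null is that a randomly chosen PT patient and a randomly chosen HT patient are equally likely to have the higher charge. That is a different quantity. A dislocation or readmission counts only as a high rank, however much it costs, while a modest therapy bill carried by nearly every PT patient moves nearly every rank.

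The informative cost question is whether therapy charges are offset, or added to, by complications and unplanned care. The planned test cannot answer it. A significant result could be reported as showing that PT costs more while the trial's own mean costs show no difference, or the reverse.

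**Working it through.** **1. The plan's own figures.** $10,000 / 0.79 = $12,658 per QALY, as stated. Enrolment is 158 + 24 = 182, or 91 per arm. The abstract gives 200, which would not weaken what follows. No power, SD or unit cost is given for charges. Sidedness is not stated, so two-sided 0.05 is assumed.

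**2. What the test measures.** It measures P = Pr(PT charge > HT charge) + ½ Pr(tie), with null value 0.5. Ignoring ties, which only shrink it, the null standard error is √[(2n+1)/(12n²)] = √[183/(12 × 8,281)] = 0.043 at n = 91.

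**3. Therapy charges only.** Inputs from the protocol: about weekly visits for three months (taken as 12), none in HT without crossover, crossover planned at 15%, and 30% in the prior research it cites. Assumption: PT patients who cross over have on average 3 visits (Poisson), so a share e⁻³ = 0.05 of them have none.

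- 15% crossover: 85% of HT patients have zero charge, and 1 − 0.15 × 0.05 = 0.99 of PT patients have a positive one. P ≥ 0.85 × 0.99 = 0.84, so z ≥ 0.34/0.043 = 7.9.
- 30% crossover: P ≥ 0.70 × 0.985 = 0.69, so z ≥ 0.19/0.043 = 4.4.

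Simulation gave 100% rejection at 79 or 91 per arm with 0, 15 or 30% crossover, and 99.6% at 79 per arm even when 70% of HT patients crossed over.

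**4. All charges, with equal means.** Assumptions not in the document: $150 per visit, an average of 8 visits for HT patients who cross over, costly complications in 3% of PT patients, and $15,000–$40,000 mean cost per complication. The HT complication rate is then solved so that mean costs match.

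- At 15% crossover, mean therapy charge in PT = 0.85 × $1,800 + 0.15 × $450 = $1,597.50; in HT = 0.15 × $1,200 = $180; gap = $1,417.50.
- At $25,000 per complication, the HT rate is 3% + 1,417.50/25,000 = 8.7%. Across the settings it runs from 3% + 1,035/40,000 = 5.6% to 3% + 1,800/15,000 = 15%.
- If nothing else varies, 0.85 × 0.913 = 0.776 of HT patients still have zero charge. P ≥ 0.776 × 0.99 = 0.77 and z ≥ 0.27/0.043 = 6.3, although the means are identical.

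**5. Letting other charges vary between patients** (91 per arm, $150 per visit, 0–30% crossover, equal means):

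| SD of other charges | Mann-Whitney rejects |
|---|---|
| $0 | 100% |
| $2,000 | 51–99% |
| $5,000 | 9–39% |
| $8,000 | 6–14% |

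A Welch test of means rejected in about 4–8%. The lower ends go with high crossover and cheaper, more frequent events; the upper ends with no crossover and rare, expensive ones.

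**6. Sensitivity** (15% crossover, events in 5% of HT patients only, equal means), at SD $2,000, $5,000 and $8,000:

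- $75 per visit: 39%, 7%, 6%.
- $150 per visit: 96%, 25%, 9%.
- $300 per visit: 100%, 86%, 51%.
- $150 per visit, with other charges varying only between seven sites: 99.6%, 67%, 37%.

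With HT mean cost 1.25 times PT's at $150 per visit, rejection was 100% with no other variation, 95% at SD $2,000 and 23% at $5,000.

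**The case against.** **Therapy-only charges.** On this reading mean charges cannot realistically be equal, and a t-test or bootstrap would also find PT dearer almost every time. This stands: the rank test is not the cause there, and the fault is that only therapy is costed.

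**The stronger inference.** A reader might infer that a significant result is certain before enrolment even when mean cost is equal or higher in HT. The document does not support that. Equal means require charges beyond therapy, and the document gives neither their components nor their spread. Implants differ by surgeon across seven sites, so other charges could vary widely. Near certainty is lost once their SD clearly exceeds about 1 to 1.5 times the mean PT therapy charge ($1,800 here).

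**The scenarios are constructed.** Equal means needed an HT complication rate about two to five times the PT rate (5.6–15% against 3%), while the Background expects more stress fractures and instability in PT. This stands as a limit on likelihood. It does not rescue the test, because a cost comparison should be able to show either direction.

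**Means would be visible anyway.** The cost-per-QALY figure uses average cost, so a reader would see means beside the p-value. That softens the harm, but the stated inference still concerns a different quantity.

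**Tests of means are imperfect too.** With rare, costly events confined to HT and no other variation, the Welch test rejected in about 7–24% of runs at equal means. This stands, and is a reason to report an interval and not to lean on a p-value.

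**A condensed article.** Detailed costing may sit in a fuller plan. That excuses a missing component list. It does not excuse the test, which the article states.

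**Conclusion.** The concern holds in a conditional form. The protocol names one test for a mean-cost hypothesis, and that test does not compare means. If charges are therapy charges, the result is practically fixed by assignment under any method and shows only that PT patients attended therapy. If charges cover all care, the rank test can declare PT dearer when mean cost is equal or higher in HT. At equal means, how often that happens runs from 100% down to near the nominal 5%, depending on visit price, event costs and the spread of other charges, none of which the document gives. The $150 visit price, the complication rates and costs, and the visit counts after crossover are all assumptions. This is a secondary aim, so the change is advisable and does not affect the primary analysis.

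**What to change.** In Quality of life and cost analysis, replace the Mann-Whitney test of charges with wording such as: *The cost comparison is the difference in arithmetic mean total cost per randomised patient (PT minus HT), with a bootstrap 95% confidence interval resampled within arm. Therapy charges alone are described by arm without a p-value.*

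Define total cost as the sum of:

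- therapist visits counted in both arms, including HT patients who cross over;
- complications;
- unanticipated presentations within the recorded window, which Table 2 sets at 90 days for events unrelated to surgery.

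**Cost of the change.** The wording and code are minor. The data work is not nil: therapist visits are named only for the PT group, so visits by HT patients who cross over must be captured. Only physical therapy prices have a named source, so unit costs for complications and unplanned care must be found. The interval will be wide, because a few expensive events drive it.
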